### **5.6.2 Blinding**

This study will be performed in a double-blind fashion. The investigator, study staff, subjects and monitor will remain blinded to the treatment until study closure. The investigational drug and its matching placebo are indistinguishable and will be packaged in the same way.

With the exceptions described in this section, the randomization list will not be available to the investigator, study staff, subjects and monitors.

The randomization list will be made available to the pharmacist preparing the study drug, to an individual responsible for dosage adjustments and to statisticians or programmers involved in preparing blinded summaries, graphs and listings to support the dose decisions.

The summaries, graphs and listings provided by the statisticians or programmers will be produced in an area to which other team members do not have access. In addition a single non blinded CHDR staff member unconnected to the study will receive reports on the haemoglobin and haematocrit of the subjects. This individual will be responsible for the dosage adjustments.

The investigator will receive a set of sealed emergency codes to be broken in case of emergency situations. If the identity of the study drug administered needs to be known in order to manage the subject's condition i.e., in case of a medical emergency or in the case a SUSAR occurs, the treatment emergency code for that subject may be broken and the study drug identified. All such occurrences should be documented in the study file. Treatment emergency codes should not be broken except in emergency situations and, if possible, the investigator should be contacted before the emergency code is opened. Just prior to database lock the unused emergency code labels will be checked and a statement to the effect that all are intact (or not as the case may be) will be made on the database lock form.

## 6 STUDY ENDPOINTS

### 6.1 Efficacy endpoints

Efficacy will be assessed at the time points indicated in the Visit and Assessment Schedule (Table 1).

Efficacy will be assessed by:

- performance in *exercise tests*
- performance in a *competition*
- measuring markers from the haematological module of the *Athlete Biological Passport*
- measuring *blood flow*

#### *Exercise tests*

All subjects will breathe during the exercise test through a facemask that will be connected to an oxymeter to collect inspired and expired gasses for analyzing:

- Oxygen consumption,  $V_{O_2}$  (L/min)
- Carbon dioxide production,  $V_{CO_2}$  (L/min)
- Respiratory minute ventilation,  $V_E$  (L/min)
- Tidal volume,  $V_t$  (L)
- Respiratory frequency,  $R_f$
- Maximal oxygen consumption,  $V_{O_{2,max}}$  ( $ml\ kg^{-1}\ min^{-1}$ )

During the exercise tests blood will be collected at predetermined stages to measure:

- Lactate levels
- Tissue plasminogen activator
- Creatinine phosphokinase
- C-reactive protein levels

$V_{O_2}$  and  $V_{CO_2}$  will be used to calculate:

- Ventilatory equivalent for oxygen ( $V_E/V_{O_2}$ ),  $eqV_{O_2}$
- Ventilatory equivalent for carbon dioxide ( $V_E/V_{CO_2}$ ),  $eqV_{CO_2}$

these values will be used to determine:

- Ventilatory threshold 1, VT1
- Ventilatory threshold 2, VT2

Physiological parameters that will be determined at VT1 and VT2:

- Oxygen consumption,  $V_{O_2}$  (L/min)
- Oxygen consumption per kg,  $V_{O_2}$  (L/min/kg)
- Percentage of maximal oxygen consumption,  $\%V_{O_{2,max}}$  (L/min)
- Power output,  $P$  (J/s)
- Power output per kg,  $P$  (J/s/kg)

Physiological parameters that will be determined at maximal effort:

- Maximal oxygen consumption,  $V_{O_{2,max}}$  (L/min)
- Maximal oxygen consumption per kg,  $V_{O_{2,max}}$  (L/min/kg)
- Maximal power output,  $P_{max}$  (J/s)
- Maximal power output per kg,  $P_{max}$  (J/s/kg)
- Lactate values

Other determinations:

- Lactate threshold 1, LT1
- Lactate threshold 2, LT2
- Cycling economy, CE ( $W\ L^{-1}\ min^{-1}$ )
- Gross efficiency, GE (%)

- Heart rate (bpm)
- Systolic blood pressure (mmHg)
- Diastolic blood pressure (mmHg)

### *Competition*

Exercise parameters that will be measured and calculated during the competition:

- Result in the race
- Total time of the race
- Power (W)
- Heart rate (bpm)
- Systolic blood pressure (mmHg)
- Diastolic blood pressure (mmHg)

Before and after the competition blood will be collected to determine if certain protein concentrations are influenced by NeoRecormon such as:

- Lactate
- Tissue plasminogen activator
- Creatinine phosphokinase
- C-reactive protein
- Coagulation and activation markers (D-Dimer, F1+2, p-Selectin, e-Selectin, ThromboxaneB2, bTG, PF4, thrombomodulin)

In urine:

- Proteinuria

### *Athlete Biological Passport*

The following Markers are considered within the ABP Haematological Module:

- Haematocrit (Ht)
- Haemoglobin (Hb)
- Red blood cell (erythrocyte) count (RBC)
- Red blood cell mass (RCM)
- Reticulocytes percentage (RET%)
- Reticulocyte count (RET#)
- Mean corpuscular volume (MCV)
- Mean corpuscular haemoglobin (MCH)
- Mean corpuscular haemoglobin concentration (MCHC)
- Red cell distribution width (standard deviation) (RDW-SD)
- Immature reticulocyte fraction (IRF)

Further calculated markers specific to the Haematological Module include OFF-hr Score (OFFS), which is a combination of Hb and RET%, and Abnormal Blood Profile Score (ABPS), which is a combination of Ht, Hb, RBC, RET%, MCV, MCH, and MCHC.

### *Blood flow*

LSCI measures:

- basal blood flow
- blood flow upon occlusion-reperfusion
- Blood flow after 'exercise'

## **6.2 Safety endpoints**

*Safety measurements before NeoRecormon/placebo administration*

Safety will be assessed by:

- ❖ Monitoring vital signs
  - o Pulse Rate (bpm)
  - o Systolic blood pressure (mmHg)
  - o Diastolic blood pressure (mmHg)
  - o Temperature measurements (°C)
- ❖ Electrocardiogram (ECG) (at rest)
  - o Heart Rate (HR) (bpm), PR, QRS, QT, QTcB
- ❖ Clinical Laboratory Assessments
  - o Haematology
    - Ht must be <52%. If Ht level is ≥52%, therapy should be interrupted until the Ht level begins to fall.*
    - Hb must be below 1.15\*Initial Hb (see Figure 1). If Hb is above that level, dosage should be interrupted until the Hb concentration falls back into the range. Then the dosage should be restarted at 2000IU/week of the previous dose.*
  - o Chemistry
  - o Urinalysis
  - o Coagulation

In addition a single non blinded CHDR staff member unconnected to the study will receive reports on the Hb and Ht of the subjects. This individual will be responsible for the dosage adjustments.

Procedure for dosage adjustment:

When the Hb and/or Ht exceeds a certain value (see 5.3) the dose adjustment officer will issue a request for a dosage change for the subject that requires the change. This request will be for the subject that requires the change in treatment but will also be issued to a random placebo subject to preserve the blinding of the study.

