**16. Safety endpoints**

Safety will be assessed by:

1. Physical examination
2. Monitoring vital signs
  - Pulse Rate (bpm)
  - Systolic blood pressure (mmHg)
  - Diastolic blood pressure (mmHg)
  - Temperature measurements (°C)
3. Electrocardiogram (ECG)
  - Heart Rate (HR) (bpm), PR, QRS, QT, QTcB
4. Clinical Laboratory Assessments
  - Haematology
 

*Ht must be <52%. If Ht level is ≥52%, therapy should be interrupted until the Ht percentage begins to fall.*

*Hb must be below a certain level (see Figure 1). If Hb exceeds that level, therapy should be interrupted until the Hb concentration falls back into the range.*
  - Chemistry
  - Urinalysis
  - Coagulation
5. Collection of treatment-emergent (serious) adverse events ((S)AEs)

*1-4 will be assessed during screening, 2-5 will be assessed at each clinical visit and before the competition. 2 and 3 will be assessed before and during the exercise tests.*

*(Serious) Adverse Events ((S)AEs) will be collected throughout the study.*

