### **19. Statistical methodology**

All efficacy endpoints will be summarized (mean and standard deviation of the mean, median, minimum and maximum values) by treatment and time, and will also be presented graphically as mean over time, with standard deviation as error bars. Change from baseline results will be utilized in all data summaries. All categorical efficacy endpoints will be summarized by frequencies. The PD endpoints will be analyzed separately by mixed model analyses of variance with treatment, time and treatment by time as fixed effects, with subject and subject by time as random effect, and with the (average) baseline value as covariate for recurring measurements and a one-way ANCOVA with treatment and baseline as covariates for measurements done at baseline and the end of the treatment period.

[figure not shown]

**Figure 1.** This dosing schedule must be applied before every administration of NeoRecormon/placebo during the 8 week treatment period. Ht = haematocrit, Hb = haemoglobin

Table 1. Visit and Assessment Schedule.

|                                                      | SCR +
training | Baseline
measurements | Treatment and exercise test weeks*               |                                                                                      |                 |              |                                                  |           |                                  | Competition week      |                       |                      | FU             |
|------------------------------------------------------|-------------------|--------------------------|--------------------------------------------------|--------------------------------------------------------------------------------------|-----------------|--------------|--------------------------------------------------|-----------|----------------------------------|-----------------------|-----------------------|----------------------|----------------|
|                                                      |                   |                          | 1, 3, 5, 7                                       |                                                                                      | 2, 4, 6, 8      |              |                                                  |           |                                  | 9                     |                       |                      | 12             |

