## **1.4 Study rationale**

### **1.4.1 Benefit and risk assessment**

NeoRecormon is a registered drug. The safety profile of this compound is known. Because side effects might occur and anaphylactoid reactions were observed in isolated cases ( $\leq 1/10.000$ ) (see SmPC, appendix 1), the study drug administrations will be done in the clinic under medical supervision. Subjects will be closely monitored and will only be discharged from the unit if their medical condition allows this.

Subjects will receive a dose of 2000, 5000 or  $\geq 6000$  IU with a maximum of 10.000 IU/week of NeoRecormon once a week for 8 weeks. The dosage depends on haemoglobin (Hb) concentration

and haematocrit (Ht) measured prior to administration. If Ht is  $\geq 52\%$  dosage will be interrupted. If Ht is  $< 52\%$  the dosage depends on the Hb concentration (see Figure 1).

The effects of NeoRecormon used in patients in an autologous blood predonation programme most closely resembles the effects of NeoRecormon in healthy volunteers. For the use of NeoRecormon in an autologous blood predonation programme, the SmPC (see appendix 1) states that the maximum dose should not exceed 1200IU/kg (or 90.000 IU for a 75kg subject) per week for subcutaneous administration. Planned doses of 2000IU, 5000IU or  $\geq 6000$  IU with a maximum of 10.000IU/week of NeoRecormon will be well below this maximum dose and are therefore considered safe. The risk is considered small and therefore acceptable compared to the scientific benefit.

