### **Stopping criteria**

Dosing will be interrupted if

- Ht  $\geq$  52%
- Hb exceeds the upper limit of the target range (see Figure 1)
- there's an unacceptable tolerability profile based on the nature, frequency, and intensity of observed AEs

These criteria will be maintained by the non-blinded CHDR staff member unconnected to the study.

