#### *Additional safety measures*

A single non-blinded CHDR staff member unconnected to the study will receive reports on Hb concentration and Ht of the subjects. This individual will be responsible for the dosage adjustments. If Ht exceeds 52% in a subject, dosage will be stopped and if necessary, ±0.5L blood will be collected from that subject to rearrange a normal Ht percentage. This subject will then be excluded from the study.

(Serious) Adverse Events ((S)AEs) will be collected throughout the study.

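### The protocol gives three different outcomes for a subject whose haematocrit has passed 52%: restart once it starts falling, hold while it is 52% or more, or stop and exclude

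*Protocol*

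**What the plan says.** The protocol addresses Ht at or above 52% in several places.

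- **Section 6.2, measurements before administration.** Ht has to be under 52%. At 52% or more, "therapy should be interrupted until the Ht level begins to fall". Synopsis section 16 has the same rule: "therapy should be interrupted until the Ht percentage begins to fall". Neither names a level at which dosing resumes.
- **Section 6.2, the haemoglobin (Hb) rule in the same bullet.** Above 1.15 times the initial Hb, "dosage should be interrupted until the Hb concentration falls back into the range". This restart condition is a level.
- **Section 1.4.1.** Dosing is interrupted at Ht of 52% or more. Only below 52% is a dose chosen, from Hb and Figure 1.
- **Section 1.4.6, stopping criteria.** The list opened by "Dosing will be interrupted if" includes Ht of 52% or more. It gives no restart condition for Ht.
- **Section 6.2, additional safety measures.** "If Ht exceeds 52% in a subject, dosage will be stopped and if necessary", about half a litre of blood is drawn. The paragraph ends: "This subject will then be excluded from the study". Section 7.2.1 repeats this rule.
- **Figure 1 legend.** "This dosing schedule must be applied before every administration of NeoRecormon/placebo during the 8 week treatment period". The figure itself is not in the text reviewed.

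**The concern.** A fall is a comparison of two readings and says nothing about where the second one lies. The ending clause in section 6.2 and synopsis section 16 can therefore be met while Ht is still at or above the limit that the same bullet sets. The neighbouring Hb rule does not have this problem, because it waits for a return to the range.

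Other sections attach different consequences to the same reading: continued hold in one group, permanent stop and exclusion in another. Nothing says which prevails. The decision rests with one unblinded staff member who is not part of the study team (synopsis section 17, section 5.6.2), while the investigator is blinded. That person needs a single rule.

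Two things are at stake. One is the conduct of the protocol's only numeric Ht safety limit. The other is who stays on treatment and contributes to the later ramp tests, the time-to-exhaustion test and the race, since restart, hold and exclusion lead to different exposure and different follow-up.

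**Working it through.** No plan figure has to be reproduced; the check is a comparison of text. Take two successive pre-dose readings of 54% and then 53%. These values are illustrative and do not come from the documents.

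| Place | At 54% | At the next reading, 53% |
|---|---|---|
| Section 6.2 main bullet; synopsis section 16 | Interrupt | Ht has started to fall, so the ending clause is met; yet 53% still breaches the under-52% requirement in the same bullet |
| Section 1.4.1 | Interrupt | Still 52% or more: interrupt; no Hb-based dose described at this level |
| Section 1.4.6 stopping criteria | Interrupt | Still 52% or more: interrupt |
| Section 6.2 additional safety measures; section 7.2.1 | Above 52%: stop and exclude | No further dosing |

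The boundary also differs. The interruption rules start at 52% or more, and the exclusion rule starts above 52%. A reading of exactly 52% therefore leads to interruption without exclusion, and any fall from there is below the limit. On that narrow reading the ending clause and the exclusion rule could coexist. The protocol does not say this, and section 6.2 and synopsis section 16 apply temporary interruption to every Ht of 52% or more.

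**Does the Hb ceiling make the Ht wording irrelevant?** Inputs: entry Ht below 48% (section 4.3) and the Hb ceiling of 1.15 times the initial value (section 6.2). Assumption, not in the documents: Ht rises in proportion to Hb.

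- Entry Ht at which 52% coincides with the Hb ceiling: 52 / 1.15 = 45.2%.
- Entry Ht at which 53% coincides with the Hb ceiling: 53 / 1.15 = 46.1%.

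Under this assumption, a subject who entered below 45.2% crosses the Hb ceiling before Ht reaches 52%. A subject who entered between 46.1% and 48% could read 53% with Hb still within its ceiling, so only the Ht wording would decide. The Hb rule covers part of the eligible range and leaves the rest uncovered.

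**The case against.** The strongest reply is that the protocol never lets a dose through at 52% or more. The trigger in section 6.2 and synopsis section 16 is a standing one: a 53% reading meets it afresh, whatever the trend. The rule sits under measurements made before administration, the Figure 1 legend has the schedule applied before each dose, and sections 1.4.1 and 1.4.6 interrupt at 52% or more without qualification. In addition, section 7.2.1 and the additional safety measures in 6.2 exclude anyone above 52%, which covers the 54%-then-53% example. Figure 1, the detailed schedule, may already settle the matter.

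Much of this stands. A reader might infer that the protocol authorises injections at Ht of 52% or more. The documents do not support that: a restrictive reading is available in the same pair of sentences, and the exclusion rule points the same way. The restart wording also cannot be treated apart from the exclusion rule, because that rule decides whether a restart question arises at all.

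The reply does not remove the inconsistency. If the pre-dose check always governs, the ending clause in 6.2 and synopsis section 16 has no work to do for readings still at or above 52%. If exclusion governs, temporary interruption is wrong for every reading above 52%. Whatever Figure 1 contains, these sentences contradict one another.

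A second tempting inference is a rate. With true Ht assumed constant at 52–54% and a single-reading SD of 0.5–1.5 points, the reading after one of 52% or more is lower in 50–75% of cases, and lower but still 52% or more in 25–50%. With the 120-day red-cell lifespan in section 1.4.2 and a complete stop in production, one week lowers Ht by 7/120 = 5.8% in relative terms, so a start of 52 / (1 − 0.058) = 55.2% or more would still be at the limit a week later. These figures only illustrate that a fall need not mean a return below 52%. The true Ht values, the SDs and the production stop are assumptions, and the percentages are conditional on a first reading of 52% or more. They do not measure how many subjects or doses are affected.

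**Conclusion.** The inconsistency holds as a matter of text. For Ht above 52%, three outcomes are written: the interruption ends when Ht starts to fall (6.2 main bullet, synopsis section 16), dosing is on hold while Ht is 52% or more (1.4.1, 1.4.6), or dosing stops and the subject is excluded (6.2 additional safety measures, 7.2.1). No order of precedence is given.

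The consequence is limited to dosing conduct and to who continues on treatment. No effect on sample size or power is shown. The documents give no frequency of reaching 52%, so the size in subjects or doses is unknown. The conclusion rests on the wording alone. The proportional Ht–Hb rise is assumed only to show that the Hb ceiling would not always decide first.

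**What to change.** Reconcile the Ht interruption and restart wording in section 6.2 and synopsis section 16 with the under-52% requirement in the same bullets, section 1.4.1, the stopping criteria in 1.4.6, the additional safety measures in 6.2, section 7.2.1 and Figure 1. One stated condition should decide in every place whether a subject is held, restarted or excluded, and it should treat a reading of exactly 52% the same way throughout. Which condition is right is for the sponsor's clinicians.

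The cost is a few sentences and a check of Figure 1. No extra measurement is needed, since Table 1 already has Hb and Ht taken before each dose. Section 10.6.2 counts dose-regimen changes as substantial, so the edit may need ethics committee approval and notification from the competent authority if it is classed that way.

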**17. Blinding**

This study will be performed in a double-blind fashion. The investigator, subjects and all study staff will remain blinded. A non-blinded CHDR staff member (not part of study staff) will receive report of Hb and Ht before dosing and will follow the instruction as described in Figure 1. This individual will be responsible for the dosage adjustments.

Procedure for dosage adjustment:

When the Hb concentration and/or Ht exceeds a certain value or Hb stays below a certain value (see Figure 1) the dose adjustment officer will issue a request for a dosage change for the subject that requires the change. This request will be for the subject that requires the change in treatment but will also be issued to a random placebo subject to preserve the blinding of the study.

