##### ***Dosage Rationale***

An initial dose of 5000IU/week will be administered because previous studies showed that with this dose the above mentioned target range should be reached. If the upper limit of the target range is exceeded the dose will be interrupted until the Hb concentration falls back into the range. At that point, therapy should be restarted at 2000IU/week. If treatment weeks  $\geq 5$  and  $Hb < (1.10 \times \text{Initial Hb})$  the dose will be adjusted to  $\geq 6000$  IU/week (maximal 10.000IU/week), so that it is still possible to reach the target range within 8 weeks.

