#### **1.4.7 Treatment duration**

In this study 24 subjects will be injected with NeoRecormon and 24 subjects will be injected with placebo once a week during 8 weeks.

A treatment period of 8 weeks is chosen because this will provide sufficient time to reach the target range. If the target range is not reached after 5 weeks, the dose will be adjusted. In addition, during this treatment period study objectives such as assessment of safety and efficacy can be performed adequately.

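### The sham dose-change procedure is stated in two versions and has no matched sham for restarts, so an interrupt-then-restart sequence can reveal active treatment

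*Protocol*

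**What the plan says.** The blinding procedure for dose changes appears twice in the protocol.

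- **Synopsis section 17 (Blinding)** gives two kinds of trigger: "When the Hb concentration and/or Ht exceeds a certain value or Hb stays below a certain value (see Figure 1". The dose adjustment officer then issues a request for the subject concerned, and that request "will also be issued to a random placebo subject to preserve the blinding of the study".
- **Section 6.2 (Safety endpoints)** repeats the procedure, including the copy to a random placebo subject, but with one kind of trigger: "When the Hb and/or Ht exceeds a certain value (see 5.3) the dose adjustment officer will issue a request for a dosage change". Its pointer to section 5.3 adds nothing, because 5.3 only refers on to Figure 1.

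The dosing rules produce more than one kind of change:

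- **Increase.** Section 1.4.7 states "If the target range is not reached after 5 weeks, the dose will be adjusted", and the Dosage Rationale in section 1.4.6 describes the same upward step for low haemoglobin.
- **Interruption, then restart.** The Dosage Rationale interrupts dosing above the upper limit until haemoglobin is back in range, and continues: "At that point, therapy should be restarted at 2000IU/week".

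The Figure 1 caption says of the schedule: "This dosing schedule must be applied before every administration of NeoRecormon/placebo during the 8 week treatment period". The figure itself could not be read in the copy used here.

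**The concern.** A sham request protects the blind only if whatever an observer sees on an active subject is equally likely to be seen on a placebo subject. Two features put this in doubt. First, section 6.2 is silent on low haemoglobin, so staff working from it have no instruction to pair a dose increase with a sham. Second, adjustments come in sequences, while the sham rule is written for one request at a time. Haemoglobin returning into range is not named as a trigger in either version, and nothing says that the placebo subject who received the sham interruption also receives a sham restart.

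The performance endpoints depend on effort. The ramp test runs to exhaustion (Appendix 5), the submaximal test lets the subject change the power himself (section 7.5), and there is a race (Appendix 6). If the pattern of requests lets staff or subjects infer treatment, the comparison of the arms loses the protection that the double-blind design is meant to give.

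**Working it through.** The protocol gives no figure for blinding, so there is nothing to reproduce. The check compares the two texts and then asks what an observer of the requests could infer.

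**Inputs.** There are 24 placebo and 24 active subjects: "24 subjects will be injected with NeoRecormon and 24 subjects will be injected with placebo once a week during 8 weeks" (section 1.4.7). Each request is copied to one placebo subject (synopsis section 17 and section 6.2). The number of interrupted active subjects, k, is not given, so it is varied.

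**Step 1: coverage by type of change**

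| Change | Synopsis 17 | Section 6.2 |
|---|---|---|
| Interruption, limit exceeded | request and sham | request and sham |
| Increase, haemoglobin stays low | request and sham | not mentioned |
| Restart, haemoglobin back in range | not mentioned | not mentioned |

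**Step 2: a single covered request.** One active and one placebo subject receive it, so P(active | request) = 1/(1 + 1) = 50%. The blind is protected.

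**Step 3: interruption then restart, with no sham for the restart.** No placebo subject shows the sequence, so P(active | sequence) = k/(k + 0) = 100%.

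**Step 4: the same sequence, with a sham restart sent to a newly drawn placebo subject.** The second draw hits the subject from the first with probability 1/24 = 4.2%. For k = 1, P(active | sequence) = 1/(1 + 1/24) = 24/25 = 96%. For larger k, unrelated draws can combine by chance into a plausible sequence. A simulation of 20,000 runs assumed interruptions in weeks 3 to 6, restarts 1 to 2 weeks later, draws with replacement and an observer who sees every request. With m the mean number of placebo subjects showing an interruption before a restart, P = k/(k + m):

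| k | m | P(active given sequence) |
|---|---|---|
| 3 | 0.285 | 3/3.285 = 91% |
| 6 | 0.968 | 6/6.968 = 86% |
| 12 | 3.092 | 12/15.092 = 80% |

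**Step 5: the same sequence, with a matched partner.** If the placebo subject given the sham interruption also gets the sham restart, but partners may be drawn twice, then m = 2.876, 5.401 and 9.621 for k = 3, 6 and 12. This gives 3/5.876 = 51%, 6/11.401 = 53% and 12/21.621 = 56%. Drawn without replacement, m = k and the probability is k/(2k) = 50% for any k. With 24 per arm there are enough partners even if every active subject needs one.

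**Step 6: increases.** Under synopsis 17 an increase is paired, so the probability is 50%. If increases were issued without a sham because section 6.2 names none, and only active subjects triggered them, it would be 100%. The caption of Figure 1 suggests a third possibility, that the schedule is applied to placebo subjects' own values. Assume that haemoglobin on placebo changes by 0% on average, with a standard deviation of 2% to 5%. The share below 1.10 times the initial value is then Φ(10/SD), from Φ(10/5) = 97.7% to Φ(10/2) > 99.9%. Increases would then be common on placebo and would mark nobody.

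**The case against.** The strongest reply is that every request the protocol describes is paired, since request and sham share one trigger in both versions. Read strictly, section 6.2 leaves the low-haemoglobin request out; it does not order an increase without a sham. That is right. A reader might infer that every dose increase identifies an active subject, but this needs section 6.2 to override synopsis 17 and needs only active subjects to trigger changes, which the Figure 1 caption puts in doubt. What stands is a contradiction to be reconciled.

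Second, the text says a random placebo subject. It does not say that a new one is drawn at each step, so the figures in Step 4 rest on one reading. Nor does it say that one subject is kept throughout, and a rule worded per request leaves this to whoever carries it out.

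Third, visibility is not established. Section 5.6.2 gives the pharmacist and the dose adjustment officer the randomization list, syringes are identical or covered (section 5.1), and a change of dose level need not show at injection. The protocol does not say which blinded staff see requests, or whether an interruption means no injection or a dummy one. This limits the size of the problem without removing it: a sham would serve no purpose if only unblinded people saw requests.

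Fourth, it is tempting to say that only active subjects show complete sequences, or that an interruption never restarted gives away a placebo subject. Neither holds. With k = 12 and fresh draws, about three placebo subjects show a complete sequence. An active subject may also stay interrupted, because haemoglobin is not yet back in range, haematocrit passes 52% and the subject is excluded (sections 6.2 and 7.2.1), or dosing stops for other reasons (section 4.6.1).

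Finally, section 3.1.5 asks subjects at follow-up which treatment they believe they had. That is a partial check on their own blinding, after the fact, and it does not cover staff.

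**Conclusion.** The point holds as an inconsistency and a gap. Synopsis 17 and section 6.2 disagree on whether low haemoglobin triggers a sham, and neither provides a matched sham for the planned restart. If requests or missed injections are visible to blinded people, an interrupt-then-restart sequence indicates active treatment with probability 100% when the restart has no sham. With a fresh draw the figure is about 80% to 96%, where k and the timings are assumptions. A matched partner would bring it to 50%.

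A reader might go further and conclude that the sham procedure fails altogether. The protocol does not support that, because a single exceeded-limit request is paired one to one. Nor does it support a statement about the direction or size of bias in the performance endpoints: who sees the requests is not stated, and the conduct of the exercise tests is left to a manual. The point is worth acting on because the endpoints depend on effort and the remedy is nearly free.

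**What to change.** 1. Reconcile the trigger in section 6.2 with synopsis section 17, so that both give the same list of events that lead to a request with a sham, and the list covers every type of dose change the protocol plans, including the restart.
2. State whether Figure 1 is applied to placebo subjects' own values or whether placebo subjects receive sham requests only.
3. Replace the random placebo subject with a matched partner. At an active subject's first request, draw one unused placebo subject at random, without replacement. That partner then receives sham versions of all later requests for that active subject (interruption, restart, increase) at the same visits. The unblinded dose adjustment officer keeps the pairing list.
4. State that exclusions for safety under sections 6.2 and 7.2.1 are not mirrored.

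No dose rule for active subjects changes. The cost is an amended paragraph, a short list kept by someone who already holds the randomization code, and some omitted or relabelled saline injections on placebo.
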